## Abstract

**Background:**

Lasers have wide applications in medicine but are associated with pain and anxiety, particularly in younger patients. Pain mitigation is often limited to topical anesthetics in the outpatient setting. Distraction techniques are limited by the need for ocular protection, which can include eye patches that completely occlude vision. Virtual reality (VR) is effective at managing procedural pain and anxiety during other short medical procedures and is a promising tool for this population.

**Objective:**

This trial aims to assess the safety, feasibility, and efficacy of the virtual reality pain alleviation therapeutic (VR-PAT) for pain management during outpatient laser procedures.

**Methods:**

A total of 40 patients requiring outpatient laser therapy for at least 2 sessions will be recruited from a pediatric hospital in the Midwestern United States for this crossover randomized, 2-arm clinical trial. During the first laser visit, the participants will be randomly assigned to either play the VR-PAT game during their procedure or wear the headset with a dark screen. Participants will answer questions about their pain (Numeric Rating Scale 0‐10), anxiety (State-Trait Anxiety Inventory for Children, Numeric Rating Scale 0‐10, and Modified Yale Preoperative Anxiety Scale), and pain medication usage. Those playing the VR-PAT will report simulator sickness symptoms and their experience playing the game. At their second laser visit, participants will cross over to the opposite intervention. The primary outcomes are the differences in self-reported pain and anxiety between the 2 interventions. Feasibility outcomes include the proportion of screened patients who were eligible, have given consent, and completed both visits, as well as adverse events reported. To evaluate the efficacy of pain reduction, composite pain scores, and pain medication usage will be calculated for each laser visit. To evaluate the efficacy of anxiety reduction, the change in Modified Yale Preoperative Anxiety Scale scores will be compared between control and VR groups at each visit using the Wilcoxon rank sum tests. All statistical analyses will follow the intention-to-treat principle with regard to intervention assignment at each visit.

**Results:**

The study was funded in January 2023 and began enrollment at that time. A total of 44 participants were recruited, and data collection was completed in November 2025, with 40 participants completing both visits. The sample was balanced, with 40 participants using the intervention and participating in the control condition. The age range of the complete sample was 6 to 21 years at recruitment, and 22 (55%) were female. Data analysis is in progress with final results planned for June 2026.

**Conclusions:**

Findings from this innovative randomized clinical trial will provide early evidence on the efficacy of the VR-PAT in reducing self-reported pain and anxiety during outpatient laser procedures. The results from this trial will inform a large-scale, multisite study.

## Introduction

### Background and Significance

Lasers have wide applications in medicine and dermatology. In pediatric patients, laser technology is often used to treat congenital and acquired skin conditions. Pulsed dye laser (PDL) is the standard of care for the treatment of vascular birthmarks, primarily port-wine stains and capillary malformations. This laser is also used to treat infantile hemangiomas (including residual changes and ulceration), spider angiomas, and pyogenic granulomas. Additionally, lasers have become a critical component in the treatment of scars resulting from burns, trauma, surgery, and inflammatory conditions. Apart from vascular lasers, such as PDL, ablative lasers, such as the fractional CO_2_ laser, are used to improve the size, texture, symptoms, and functional limitations caused by scars.

Though it is an effective and important treatment modality in pediatric dermatology, laser therapy is often associated with significant pain for the patient [1,2]. Pain associated with laser procedures is typically described as a heat or burning sensation. PDL is described as feeling like a hot rubber band snapping on the skin with each pulse [3], and the laser pulses 15 to 100 times per treatment session [4]. Infants and young children may require some form of anesthesia [3], and even adolescents and adults may have difficulty tolerating the procedure [5].

It is vital to mitigate pain and anxiety during laser procedures in pediatric patients. Unrelieved pain during pediatric procedures has been associated with adverse effects on recovery and postoperative behavioral abnormalities [6-8], including postprocedural symptoms of posttraumatic stress disorder [9]. Anxiety and pain can lead to a lack of cooperation with the procedure by the patient, which may impact the effectiveness of the therapy [5]. Darkness from laser eye protection and pain-related distress may also precipitate phobic responses in the patient [4], which increases their anxiety and can negatively impact subsequent treatments [10], as well as future interactions in health care settings [11]. Experiences of undertreated pain can have significant adverse effects on immediate and long-term mental health for pediatric patients [12]. Therefore, effective pain mitigation during pediatric laser procedures is a crucial component of biobehavioral intervention targeting pediatric patients.

Pharmacologic analgesia is often the primary pain management technique during pediatric laser procedures. Topical anesthetics, often lidocaine, are the most commonly chosen analgesics during pediatric laser procedures [13]. Topical agents are generally well-tolerated in the pediatric population and can reduce pain associated with laser procedures, but they are often insufficient for pain mitigation in all patients [3]. Additionally, topical agents may not be a viable option when the lesion involves large regions of the body or is located near the ears, fingers, eyes, or nose [2]. Local injectable lidocaine is an additional pain relief option. However, epinephrine is typically included in the injected solution, which may decrease lesion size and hinder the effectiveness of the laser treatment for vascular lesions [3]. Furthermore, the use of a needle may result in increased pain or discomfort, lesion distortion, and there may be concern for lidocaine toxicity if the anesthetized area is large [5]. General anesthesia is an option that is occasionally used [13], and it can be especially useful for children who are highly uncooperative or distressed [3]. However, this option is very carefully considered due to growing concern for neurocognitive defects resulting from the use of general anesthesia in children [13,14]. Sedatives, often midazolam, can be administered to alleviate both pain and anxiety, as well as to induce anterograde amnesia [5]. Unfortunately, midazolam is associated with a primary side effect of respiratory depression, which is a serious concern [3].

It is preferable to treat dermatologic conditions as early as possible [5]; the response rate to laser procedures is significantly better in younger children [15], and delaying the procedure may negatively impact psychosocial development due to exposure to social stigma [4]. Therefore, waiting until the child has aged to maximize tolerance of the laser procedure is not ideal. Efforts must be made to minimize the pain and anxiety associated with the laser procedure for the pediatric patient.

Ocular exposure to laser radiation can result in permanent eye damage, including vision loss [5]. It is paramount that any eye protection used during the procedure effectively blocks radiation exposure to the patient’s eyes. A variety of eye protection options can be used. Eye patches fully cover the eyes and thus immerse the patient in darkness, which can induce anxiety during these laser procedures. The special eye protection needed by patients during laser treatment creates a unique opportunity to use a virtual reality (VR) headset not only as eye protection but also as a pain and anxiety management strategy.

### Gap in Knowledge

There is a clear need for the development of alternative nonpharmacologic pain and anxiety relief modalities for pediatric procedural pain. Recently, distraction has emerged as a highly effective pain-mitigation tool for this population. According to the cognitive-affective model of pain, distraction alleviates pain by consuming attentional resources that would otherwise be devoted to pain processing [16], thereby decreasing subjective pain and related distress [17]. Various forms of distraction have been found to be effective at reducing subjective pain [10,18], decreasing pain-related brain activity [19], and increasing positive procedural outcomes [20] in pediatric populations.

Among the various forms of distraction, VR has been found to be highly effective in medical settings for pediatric patients. VR uses a head-mounted display to create a highly immersive environment that blocks the sights and sounds of the hospital and can distract the user from real-world pain [11]. VR has been found to be significantly better than the standard of care at decreasing self-reported pain [21-23], anxiety [10,24], time spent thinking about pain [10,23], heart rate [18], and pain-related brain activity [25,26] during painful pediatric procedures. VR has also been found to improve cognitive and emotional processing of the event [18], and VR use reduces the formation of phobic responses to hospital environments [27].

The vast majority of these studies reported no instances of simulator sickness or other immediate adverse effects of using VR [10,25,28] and noted that the majority of patients found the VR experience to be enjoyable [23,28]. In addition, both parents and nurses tend to be satisfied with the experience of using VR on the patient [29], and nurses have reported that children are more cooperative during procedures while using VR, which improves the efficacy of the procedure itself [12]. Additionally, the effectiveness of VR-based pain relief does not seem to diminish when used repeatedly, and patients continue to find the technology fun to use [23,27]. VR is a promising anxiety- and pain-relief modality that is becoming increasingly flexible, immersive, and affordable, making it easy to use in medical settings and highly applicable to a wide variety of patients and medical settings [28].

Despite extensive research regarding VR use in medical settings, there remains a knowledge gap regarding the efficacy and safety of VR in pediatric laser procedures. Most previous studies were conducted in the context of burn wound dressing changes, IV placement, or laboratory-induced pain. We are aware of very few studies examining the use of VR in the setting of laser procedures. Jaquez et al [30] found promising early results for nonpharmacologic distraction during a variety of dermatologic procedures, but this was not exclusive to PDL or CO_2_ lasers. More research is needed to understand the potential application of VR in this setting. Additionally, little is known about the safety of using VR headsets during laser procedures. Ocular exposure to laser radiation can result in permanent eye damage, including vision loss [5]. It is paramount that any eye protection used during the procedure effectively blocks radiation exposure to the patient’s eyes.

### Prior Work

Our previous clinical study provided strong evidence regarding the efficacy of the smartphone version of the virtual reality pain alleviation therapeutics (VR-PAT) for significant pain reduction during burn dressing changes [29]. This randomized clinical trial (RCT) tested the efficacy and feasibility of this tool among 90 pediatric outpatient patients with burn injuries (aged 6 to 17 years). Participants were randomly assigned to an active VR-PAT group (n=31), a passive VR-PAT group (n=30), or a standard care group (n=29) during a burn dressing change. Active VR-PAT significantly reduced observed and self-reported pain during burn dressing changes. Patients and caregivers reported satisfaction with the VR-PAT, and nurses reported that the tool could be easily used in clinics.

In another RCT study, we examined the efficacy of VR-PAT as a pain alleviation tool during at-home dressing changes for pediatric patients with burn injuries (aged 5‐17 y) [31]. Participants (n=35) were randomly assigned to either the active VR-PAT condition or the control condition. Participants found VR-PAT to be a useful distraction during home dressing changes and reported it to be easy to implement. In the VR-PAT group, children and caregivers reported that pain decreased as the week of dressing changes progressed and was lower than that in the control group after the fourth dressing change. Children playing VR-PAT reported consistent happiness and fun as the week went on, alongside increased realism and engagement, indicating that repeated use of the tool does not diminish its efficacy.

Our previous studies and preliminary results position us well to expand the VR-PAT for anxiety relief and pain reduction during pediatric laser therapy.

### Objectives

The overall objective of this proposal is to conduct a randomized crossover clinical trial to assess the safety, feasibility, and efficacy of VR-PAT for pain management during outpatient laser procedures and to evaluate anxiety as a preprocedural key factor for pain during these procedures. Our specific aims are to (1) assess the feasibility and efficacy of VR use in reducing pain in patients undergoing dermatologic laser procedures, and (2) evaluate the impact of VR use on reducing anxiety in patients undergoing dermatologic laser procedures. Our central hypothesis is that VR-PAT is safe to use and can effectively and significantly reduce pain during pediatric dermatologic laser procedures.

## Methods

### Trial Design

We will conduct a prospective, 2-group crossover RCT with a 1:1 allocation ratio to either the intervention (VR-PAT gameplay) or the control (VR headset turned off) for the first laser appointment. Participants will crossover to the opposite group at their second laser appointment. Pain, anxiety, and VR engagement (for those in the intervention group) will be assessed after each research appointment, spaced approximately 6 to 8 weeks apart. The findings will be reported based on the CONSORT (Consolidated Standards of Reporting Trials) guidelines. This protocol is reported in accordance with the SPIRIT (Standard Protocol Items: Recommendations for Interventional Trials) guidelines (Checklist 1).

### Settings and Participants

Participants will be enrolled from the outpatient dermatology clinic on the main campus of Nationwide Children’s Hospital (NCH) in Columbus, Ohio. We plan to recruit 40 patients (aged ≥5 y) to complete 2 laser visits who clinically require laser therapy. The inclusion criteria are: (1) dermatology patients (≥5 y) undergoing the first of a new series of laser procedures at the NCH Outpatient Dermatology Clinic, (2) having a legal guardian present for patients aged less than 18 years during the procedure (for informed consent), and (3) the ability to communicate orally. Exclusion criteria include: (1) any wounds that may interfere with study procedures; (2) use of the diode laser; (3) vision, hearing, or cognitive and motor impairments preventing valid administration of study measures; (4) history of motion sickness, seizure disorder, dizziness, or migraine headaches precipitated by visual auras; (5) minors in foster care; (6) inability to communicate in English; (7) pregnant women; or (8) prisoners. The exclusion of diode laser use was determined during safety testing, in which laser safety was confirmed for PDL and CO_2_ lasers but not diode lasers. Laser safety testing was performed by a third-party company to evaluate the VR headset for ocular safety. They determined that the headset was safe to use with PDL and CO_2_ lasers but did not provide protection against diode laser wavelengths. Based on the previous studies, patients aged less than 5 years were unable to respond effectively to pain measurement and other study questionnaires.

The laser team (led by our physician champion) will identify potential study individuals, and our research associates will screen them for eligibility. Once a patient’s eligibility is confirmed, a trained researcher will approach the patient and their legal guardian (if necessary) to introduce the study. Trained research staff will ensure participants are awake, alert, and able to provide assent (if the child is >9 y but <18 y) or consent if aged ≥18 years, and demonstrate understanding of the study before being consented. According to the NCH institutional review board (IRB) policy, patients aged less than 9 years only need consent from a caregiver who is the legal guardian when the study involves only minimal risk; however, all participants will be asked for verbal assent. Signed consent and assent (if applicable) will be obtained before formally enrolling patients into the study. During the informed consent conversation, the legal guardian and the patient (if aged ≥18 y) will be asked for permission to store the participant’s protected health information and identifiable information for future IRB-approved research. The person providing consent can opt out of this option, which will not affect their standard of care treatment. Biological specimens will not be collected for this study.

### Participant Timeline

Study enrollment at NCH—patients will be recruited prior to their first sequential dermatologic laser procedure. After consent and assent (if applicable) are obtained, patients will be randomized to either the VR-PAT intervention or the control group. A research associate will collect background information, such as demographics, anxiety levels, and prior video game experience, before randomization. VR-PAT instructions will be provided to the intervention group prior to participation.

Laser procedures at NCH (n=2 visits)—patients will receive their laser procedure as usual. Participants in the intervention group will wear the Pico headset and play the VR-PAT during their procedure. Participants in the control group will receive their laser procedure while wearing the VR headset (without the game). A researcher in the laser treatment room will observe the procedure and document, for the intervention group, the amount of time spent playing the VR-PAT, whether the participant declined to use it, and the number of interruptions of VR. Following the procedure, a different researcher (blinded to the group) will ask both groups of participants about their pain experience and satisfaction with the game. This process will be repeated once for each participant, as they will cross-over to the opposite intervention group at their next laser procedure.

### Randomization and Blinding

A block randomization scheme with a block size of 4 will allocate participants to 1 of the 2 intervention sequences (VR-PAT followed by control or control followed by VR-PAT) at a 1:1 ratio without stratification. We chose a block randomization strategy to avoid imbalances in allocation to the intervention at the first visit in case we were unable to recruit our planned sample. The randomization scheme was developed and uploaded to a study-specific REDCap (Research Electronic Data Capture; Vanderbilt University) project by the project manager. Study participants are randomized into intervention sequences after signing consent and completing the baseline survey. Research recruiters and participants are not aware of the intervention assignment until the participant is randomized in REDCap.

We cannot blind the participants or the clinical team to the assigned intervention since the headset will either be turned on or off. The researcher who randomized the participant and observed the laser procedure will not be blinded, but a second researcher, who is blinded to the intervention group, will collect pain ratings and anxiety post procedure. The second researcher will wait in a different room during randomization and the laser procedure, and the first researcher will remind the participant at the end of the laser procedure to keep their group a secret until they are asked. The study biostatistician will also be blinded to the intervention group while performing analyses on the primary outcome. The data will be blinded by removing labels such as “VR” and “Control” and replacing them with unidentifiable letters (eg, “A” and “B”). The biostatistician will need to be unblinded for secondary outcomes, as only participants in the intervention group will answer the VR experience questions.

The blinded researcher will need to be unblinded after pain and anxiety ratings are obtained, as those in the control environment will not be able to answer the VR experience questions. The researcher will become unblinded by asking participants whether they played the game. The biostatistician will also be unblinded for full analyses by being provided with the full dataset, including complete data labels and VR questions. This unblinding will take place after the primary outcome analysis has been completed.

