For aim 2, the mYPAS score had 6 repeated measurements over time (T0, T1, and T2 during each of the 2 laser procedures). At the first procedure, we will compare the change in mYPAS scores from T0 to T1 and T0 to T2 between the control and VR groups using either 2-sample 1-tailed *t* tests or the Wilcoxon rank sum tests (depending on the distribution of the change in mYPAS scores). The clinical effect size will be the difference in medians of the change in mYPAS, with the confidence limits calculated by bootstrapping with replacement using 1000 repetitions. Bootstrapping has been found to provide better confidence limits with asymmetric data, such as the mYPAS score in our study, and is the recommended method. The same statistical analysis approach has been successfully used by other researchers, who reported that VR effectively reduced preoperative anxiety among 71 children aged 5 to 12 years scheduled for elective surgery [42]. At the second procedure, we will compare the mYPAS scores at T0 and T1 between the control and VR groups using the Wilcoxon rank sum tests since mYPAS scores are shown to be asymmetric [42]. The clinical effect size will be the difference in medians of mYPAS. Confidence limits will be calculated using bootstrapping again.

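### A fixed block size of 4 on one list at one open clinic leaves about a third of first-visit assignments inferable, which weakens concealment and rater blinding for the visit-1 comparisons

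*Protocol article*

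**What the plan says.** All of the allocation rules stand in the protocol article under Randomization and Blinding.

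- **List:** "A block randomization scheme with a block size of 4 will allocate participants to 1 of the 2 intervention sequences". Allocation is made "at a 1:1 ratio without stratification". The stated reason for blocking is to avoid imbalance at the first visit if recruitment fell short. The project manager made the list and uploaded it to REDCap.
- **Setting:** one site. "Participants will be enrolled from the outpatient dermatology clinic on the main campus" (Settings and Participants).
- **Who learns assignments:** "We cannot blind the participants or the clinical team to the assigned intervention since the headset will either be turned on or off". The same holds for a member of the research team: "The researcher who randomized the participant and observed the laser procedure will not be blinded". The second researcher is blinded while taking the post-procedure pain and anxiety ratings, and then: "The researcher will become unblinded by asking participants whether they played the game".
- **Safeguard:** "Research recruiters and participants are not aware of the intervention assignment until the participant is randomized in REDCap". Randomization follows consent and the baseline survey.

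Two planned analyses under Data Analysis compare separate groups at the first visit. The one for anxiety reads: "At the first procedure, we will compare the change in mYPAS scores from T0 to T1 and T0 to T2 between the control and VR". For the composite pain score, if carryover is significant, only first-procedure data are used, with a two-sample test.

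**The concern.** REDCap keeps the list out of sight. It cannot hide what earlier, openly known assignments imply about the next one. In a block of 4 with two places per sequence, the fourth assignment always follows from the first three, and the third follows whenever the first two agree. A visit-1 assignment also reveals the participant's whole sequence.

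Two things could follow. Staff who identify and approach candidates could foresee some assignments when deciding whom to approach; the laser team, which is not blinded, identifies candidates (Settings and Participants). A rater who has learned the earlier assignments in a block could foresee the next one while collecting visit-1 ratings.

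The paired VR-versus-control contrast is largely protected because every completer has both conditions. The visit-1 between-group comparisons have no such protection and rely on an unpredictable first assignment. Change in mYPAS is listed among the primary outcomes, and the Sample Size section says the estimated effects will be used to size later trials.

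**Working it through.** The article gives no figure for predictability, so there is none to reproduce. The inputs are block size 4, ratio 1:1, no stratification (Randomization and Blinding), and 44 participants recruited (Results). The 44 are taken as 11 complete blocks.

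**Share determined by earlier assignments.** With sequences A and B there are six equally likely orderings:

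| Orderings | Determined positions | Number determined |
|---|---|---|
| AABB, BBAA | 3 and 4 | 2 |
| ABAB, ABBA, BABA, BAAB | 4 | 1 |

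- Mean per block: (2 × 2 + 4 × 1)/6 = 4/3.
- Share: (4/3)/4 = 1/3, or 33.3%.
- Expected in 44: 44/3 = 14.7. The possible range is 11 × 1 = 11 to 11 × 2 = 22.

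**Best-guess success.** The rule is to name the sequence with more places left. The chance of being right at positions 1 to 4 is 1/2, 2/3, 2/3 and 1.

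- Position 3: (1/3) × 1 + (2/3) × 1/2 = 2/3.
- Overall: (1/2 + 2/3 + 2/3 + 1)/4 = 17/24 = 70.8%.
- In 44: 31.2 correct, against 22 by chance.

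Both results require an observer who knows the block size and has seen every earlier assignment in the block, in order.

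**Alternatives.** The fixed-block figures are exact. The varying-block figures come from simulating 4,000 lists of 44, with an observer who knows the possible sizes but not the current one.

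| Scheme | Determined | Best guess correct |
|---|---|---|
| Fixed 4 | 33.3% | 70.8% |
| Varying 2/4 | 10.8% | 72.1% |
| Varying 4/6 | 5.6% | 69.0% |
| Varying 2/4/6 | 4.1% | 69.9% |

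Varying the size removes most of the certainty but hardly changes guessing.

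**Worst-case illustration.** Assume that every participant with a determined assignment is shifted by d SD on the analysed outcome, always in the direction that favours VR. The visit-1 difference is then biased by 2 × d × 1/3:

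- d = 0.25: 2 × 0.25/3 = 0.17 SD.
- d = 0.5: 2 × 0.5/3 = 0.33 SD.

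With 22 against 22 the standard error is √(2/22) = 0.30 SD. In 8,000 simulated trials with no true effect, a one-tailed 5% t test rejected in about 13.5% and 27% respectively, and in 4.9% with no shift. The value of d is assumed; nothing in the article supplies it.

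**The case against.** A reader might infer that a third of assignments were known in advance and that concealment and blinding were broken. The article does not support this. It does not say that recruiters, clinic staff or the rater knew the block size, that anyone tracked the order, or that the same rater saw consecutive participants. The project manager made the list and helps coordinate the trial, but is nowhere said to recruit or rate. This objection stands, and it limits the point to a weakness.

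Other counterarguments also carry weight:

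- **Little room to steer.** Entry is tied to the first of a new laser series, so a patient cannot easily be held for a later place. From January 2023 to November 2025 is about 34 months; 44/34 is about 1.3 participants a month, so a block spans about three months and there is rarely a queue to reorder. Skipping a candidate before approach remains possible, but nothing indicates that it happened.
- **The endpoint is a change score.** Change from T0 removes much of any difference in starting anxiety, although regression to the mean can remain.
- **Limits of the rater argument.** Pain is self-reported. The article does not say which researcher scores mYPAS at T0 and T1; if it is the unblinded one, block size is irrelevant to those scores. A rater who learned the group at visit 1 and returns for visit 2 knows that assignment whatever the block size.
- **Pilot purpose.** The Sample Size section puts estimation before testing, so inflated rejection rates matter less than bias in the estimates.

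These points reduce the likely harm. They do not answer the fact that a safeguard on the list cannot prevent inference from open assignments, nor do they explain the fixed size. The wish for balance justifies blocking, and varying blocks serve that wish too.

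**Conclusion.** The weakness is real and limited. A fixed, unstratified block of 4 in an open single-clinic trial leaves on average one third of first-visit assignments (about 14.7 of 44) inferable to someone who knows the block size and follows the order. The statement that recruiters are unaware of assignments before randomization is therefore not assured for those participants. It needs qualifying, but the article gives no ground for calling it false.

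The consequence falls mainly on the visit-1 mYPAS comparison and on the composite fallback, which applies only if carryover is significant. The bias of 0.17 to 0.33 SD and the rejection rates of 13.5% to 27% are worst cases under full, one-directional steering on the analysed outcome. They are not properties of the plan; with no steering and no effect of foreknowledge on ratings, the bias is zero.

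**What to change.** **Current trial (enrolment complete, analysis in progress):**

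1. Qualify the concealment statement by saying who knew the block size and who had access to the list. Name predictability as a limitation of the visit-1 comparisons.
2. Adjust the visit-1 mYPAS comparison for the anxiety that Participant Timeline says is collected before randomization.
3. Optionally, repeat the visit-1 comparisons without the determined assignments, which the REDCap list identifies. About 44 − 14.7 = 29 participants would remain, so this can only be supportive.

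The cost is one covariate, a few sentences and at most one sensitivity analysis.

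**Any remaining allocation and the planned larger trial:** use randomly varying block sizes, for example 2, 4 and 6, not disclosed to recruiters or raters, with the list held by someone outside both roles. A new REDCap table costs almost nothing. The largest possible imbalance at stopping rises from 2 (half of 4) to 3 (half of 6). Because guessing success would stay near 70%, the rater should also be kept from learning assignments, for instance by having someone else ask the game-experience questions. That needs some extra staff time.
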